### Sample size

A total of 1911 patients (comprised of 511 prospectively included women and 1400 historical controls) would be sufficient to evaluate the primary objective. Incidence of the composite outcome is based on numbers of perinatal morbidity and mortality of MMC from 2019, combined with a literature-based estimation of the simultaneous occurrence of the perinatal comorbidities and mortality.^40^,^43^ Due to the unknown effect of COVID on perinatal and maternal outcomes,^44^ numbers from MMC of 2020–2021 are not included in the sample size calculation. This resulted in a rounded estimated composite outcome of 17%. Based on clinical experience, an effect size of 6% is expected. To detect this effect size with a power of 80% and a type I error of 5%, a group of 511 women will be invited for the prospective cohort. Of these 511 women, 464 women (90.8%) will be in the sampled study arm and 47 women (9.2%) in the non-sampled study arm. Based on clinical experience, an estimation of 80% acceptance rate for data collection in the sampled and non-sampled group was made (resulting in 372 women and 37 women respectively). Among the 372 women who agreed to data collection in the sampled group, it is expected that 90% will accept and receive eCTG monitoring (335 women) and 10% (37 women) will decline eCTG monitoring and therefore receive CTG monitoring. All 37 women in the non-sampled group will receive standard monitoring. For the retrospective cohort, a total of 1400 participants will be included (figure 3). No dropout rate is calculated, due to continuation of the study and sampling until the requested sample size (of both groups) is reached.

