### Statistical analysis

For the primary and secondary outcomes, based on the demographics, characteristics of the women and their baseline outcomes, a propensity score will be created. This will be used to correct for possible selection bias that may occur due to (1) the group of women who are offered eCTG but receive CTG (either by choice or circumstances) or (2) the retrospective and prospective nature of the study. Thus, a per-protocol analysis with propensity score adjustment will be considered. The propensity score models will include maternal characteristics (eg, age, BMI, parity, ethnicity), foetal indicators (eg, gestational age, foetal growth restriction, Doppler abnormalities) and care-related variables (eg, indication for admission, medication use, duration of hospitalisation). These covariates were selected based on clinical relevance and availability across both cohorts. For categorical outcomes, a logistic regression analysis will be applied to estimate the treatment effect corrected for the propensity score. For numerical outcome values, a general linear model will be applied with an appropriate probability distribution link function and the sandwich estimator to estimate a treatment effect corrected for the propensity score. For time-to-event outcome, a Cox proportional hazards model will be used with a sandwich estimator to estimate a treatment effect corrected for the propensity score. For the data gathered from the questionnaires, standard statistical tests will be used (χ^2^, t-test, Mann-Whitney tests) to determine a difference between the two treatment groups. A propensity score approach will be applied as well if large imbalances between characteristics are present between CTG and eCTG participants. Several sensitivity analyses are being anticipated. The combined endpoint will be analysed as separate end-points. Several subgroup analyses are investigated (eg, obesity). A p value of <0.05 is considered statistically significant unless otherwise specified. When possible, 95% CIs will be calculated for the reported measures of effect. Missing data will be evaluated and reported. Limited missing data is expected, and if missingness is less than 5%, list-wise deletion will be used. Otherwise, multiple imputation (eg, predictive mean matching) will be used. The imputation will be repeated at least 10 times and Rubin’s rule will be used to combine estimates and standard errors from the imputed data.

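### The primary logistic model names no prognostic covariate beside the propensity score, so with the usual standard error the test is conservative and a modest power gain from data already collected is forgone

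*Protocol article*

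**What the plan says.** The Statistical analysis section builds a propensity score to deal with two sources of selection bias: women offered eCTG who receive CTG, and the mix of historical and prospective data. The inputs are maternal characteristics, "foetal indicators (eg, gestational age, foetal growth restriction, Doppler abnormalities" among others) and care-related variables that include the indication for admission. For categorical outcomes, which include the primary composite, "a logistic regression analysis will be applied to estimate the treatment effect corrected for the propensity score". No covariate besides the score is named for that model. A sandwich estimator is named for the numerical and time-to-event models, but no variance method is named for the logistic one.

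The Study design section mentions inverse probability weighting as a way of using the score. That too brings the covariates in only through the model for monitoring group.

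The Sample size section gives the design inputs: "This resulted in a rounded estimated composite outcome of 17"%, "Based on clinical experience, an effect size of 6% is expected", and "To detect this effect size with a power of 80% and a type I error of 5"%, the group of invited women is set at 511, to which 1400 historical controls are added.

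**The concern.** A propensity score weights each covariate by how well it predicts which monitoring a woman received. Women enter anywhere between 23+0 and 32+0 weeks, and the composite consists of death and the major morbidities of prematurity. Gestational age at admission, growth restriction, Doppler and indication are therefore plausibly strong predictors of outcome, whatever their relation to monitoring group. A model with treatment and score alone uses them for bias correction but not as outcome predictors.

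At stake are some power and the honesty of the interval. The fitted score removes part of the chance imbalance in the covariates, so the estimate varies less than a standard error that ignores this would say. The result is a test that does not spend its full 5%.

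**Working it through.** **Inputs from the Sample size section**

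- eCTG group: 464 × 0.8 × 0.9 ≈ 335 ("it is expected that 90% will accept and receive eCTG monitoring (335 women) and 10% (37 women) will decline eCTG monitoring").
- Concurrent CTG controls: 37 who decline plus 37 not sampled = 74 ("All 37 women in the non-sampled group will receive standard monitoring").
- Historical controls: "For the retrospective cohort, a total of 1400 participants will be included". CTG total: 1474.
- Risks: 17% on CTG and 11% on eCTG, reading the 6% effect as absolute. Two-sided 5% is assumed, because sidedness is not stated.

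**Step 1: the plan's own power.** Two proportions, pooled variance under the null:

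- Events: 335 × 0.11 + 1474 × 0.17 = 36.9 + 250.6 ≈ 287. Pooled risk: 287.4 / 1809 = 0.1589.
- Null SE: √[0.1589 × 0.8411 × (1/335 + 1/1474)] = 0.02213.
- SE under the alternative: √[0.11 × 0.89/335 + 0.17 × 0.83/1474] = 0.01970.
- z = (0.06 − 1.96 × 0.02213) / 0.01970 = 0.844, so power = 80.1%.

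The stated 80% is the power of an unadjusted comparison. It claims nothing from covariates.

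**Step 2: score only against score plus predictors.** The article gives no covariate-outcome association, so it is varied. Simulation: 335 v 1474 women, marginal risks 11% and 17%, four standard-normal baseline covariates, logistic truth, 2,000 trials per scenario. The covariates are shifted between groups by 0, 0.2 or 0.4 SD. The score is a logistic model on the same four covariates, so entering all four directly is equivalent to score plus all four. Tests use the usual model SE.

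| Assumed AUC | Power, score only | Power, covariates entered | Gain (points) |
|---|---|---|---|
| about 0.63 | 79.6-80.7% | 80.7-81.9% | about 1 |
| about 0.75 | 81.8-83.1% | 85.0-86.4% | 2-3 |
| about 0.82 | 82.4-85.0% | 89.5-90.0% | 5-7 |
| about 0.88 | 83.9-84.9% | 92.6-93.0% | 8-9 |

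A second simulation design had four prognostic covariates plus four others, two of them shifted 0.2 SD, with 3,000 trials per scenario. It gave 80.5% v 82.0% at AUC 0.70, 80.2% v 83.9% at 0.75 and 81.5% v 87.0% at 0.80.

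**Step 3: under no effect.** At AUC 0.82, score-only rejects in 3.2-3.4% of trials, against 5.0-5.3% with the covariates entered. In the second design at AUC 0.80, score-only rejects in 3.5%. Its mean reported SE is 0.164 against a true SD of 0.152, and 0.164/0.152 = 1.08, so it is about 8% too wide.

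**Step 4: does the estimate itself become less precise?** At AUC 0.82 without shift, the SD of the marginal risk difference is 0.0199 unadjusted, 0.0186 score-only and 0.0180 with covariates. The last two differ by about 3% (0.0186/0.0180 = 1.03). At AUC 0.63 they are 0.0193 and 0.0192. On the log-odds scale the covariate model has the larger SE (about 0.215 v 0.186), because it targets a larger conditional effect (mean −0.65 v −0.54).

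**Step 5: how much is the SE?** In a close analogue of the AUC 0.80 case (1,500 trials), score-only with the usual SE has 80.2% power and 3.5% null rejection. The same estimator with an SE that allows for the estimated score has 84.3% and 5.2%. Covariates entered directly give 86.2% and 5.4%. So (84.3 − 80.2)/(86.2 − 80.2) = 4.1/6.0, about two thirds of the gap, comes from the SE.

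**The case against.** The strongest reply is that nothing promised is lost. The sample size rests on an unadjusted comparison, and score-only adjustment gave about 80-85% power in these simulations. The named predictors are score inputs, and at AUC 0.82 the score alone delivers most of the fall in the SD of the risk difference (0.0199 to 0.0186, out of 0.0199 to 0.0180). Step 5 shows that much of the power gap disappears once the SE allows for the estimated score. The article does not say that the usual SE will be used, and a fuller analysis plan may settle this. All of that stands, and it limits the point to a modest gain.

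It does not remove the point. The outcome model is stated rather than left open, and the only covariate it names is the score. Reading the score as weights does not bring the predictors in as outcome predictors either. With an SE that allows for the estimated score, weighting reached 90.6% power at AUC 0.82 without covariate shift, but only 80.9% with a 0.4 SD shift, where direct adjustment held 90.0%.

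A reader might also infer that, with 1400 of 1474 controls (95%) historical, score plus covariates is safer because it is valid if either model is right. That does not follow. In a constructed example with a correct propensity model and a misspecified outcome model, the true risk difference was 0.017. Standardising the score-plus-covariate model gave 0.075, the same as score-only, while weighting gave 0.017.

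**Conclusion.** The point holds as a forgone improvement, not as an error in the design. As stated, the primary model uses strong baseline predictors only through a score aimed at monitoring group. With the usual SE, the interval is somewhat too wide and the test rejects in about 3-4% of trials under no effect when predictors are strong. The forgone power is roughly 1 to 5 points at AUCs of about 0.65 to 0.80, and more above that.

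This rests on an assumed prognostic strength, assumed covariate shifts between groups, a main-effects logistic truth and the usual model SE. None of these is a figure from the article.

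Three stronger readings are not supported:

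- That the trial is underpowered: the 80% reproduces and is met.
- That the predictors are ignored: they are in the score.
- That real precision is lost: the SD of the risk difference changes by a few per cent at most over that AUC range.

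**What to change.** In the Statistical analysis section, keep the propensity score and add pre-specified predictors, as known at admission, to the primary logistic model: gestational age at admission (continuous), foetal growth restriction, Doppler abnormality and indication for admission. Fix the list before outcomes are compared. Only baseline variables belong here. Duration of hospitalisation, which the score lists, is not known at admission and should not be among them.

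Report the standardised risk difference beside the conditional odds ratio, with a bootstrap confidence interval that re-estimates the score in each resample. This puts the result on the scale of the planned 6-point effect and lets the interval reflect that the score is estimated.

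If validity under either a correct propensity model or a correct outcome model is wanted, use a doubly robust estimator such as augmented inverse probability weighting. It fits the weighting named in the Study design section.

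Cost: a few sentences of analysis text and slightly more programming. No further data or patients are needed, and about 287 expected events are enough for these covariates. The one drawback is that the odds ratio becomes conditional on the covariates, which is why the standardised risk difference should accompany it.

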### Study objectives

The primary objective of the study is to evaluate the effect of continuous antepartum eCTG monitoring on severe perinatal morbidity and mortality, by comparing with conventional intermittent CTG monitoring. The objectives are investigated in preterm fetuses (GA 23–32 weeks) whose mothers are admitted to the OHC. The primary study outcome is a composite outcome consisting of (1) Perinatal mortality, defined by the WHO as: deaths that occur after a gestational age of ≥22 weeks or, if unknown >500 gram, until 28 days after birth^20^ and (2) Major neonatal morbidity assessed at the time point when the neonate is discharged from the hospital.^21^ Major neonatal morbidity is defined as either: intraventricular haemorrhage (IVH) grade three or more,^22 23^ periventricular leukomalacia (PVL) grade two or more,^24 25^ moderate or severe bronchopulmonary dysplasia (BPD),^26^,^28^ necrotising enterocolitis (NEC) grade two or more,^29 30^ or retinopathy of prematurity (ROP) necessitating laser therapy.^31^ Secondary study objectives are the effect of continuous antepartum eCTG compared with conventional intermittent CTG monitoring on maternal mortality, neonatal morbidity, satisfaction for both patient and caregiver, duration of pregnancy, the need to switch between monitoring methods (either from eCTG to CTG or vice versa), timing and number of obstetric interventions, duration of admission at the OHC and admission and duration of admission at the neonatal intensive care unit. Demographics will be obtained from the electronic patient file. The secondary outcomes are defined as follows: maternal mortality as defined by the WHO^32^: any death from any cause related to or aggravated by pregnancy or its management (excluding accidental or incidental causes) during pregnancy and childbirth or within 42 days of termination of pregnancy, irrespective of the duration and the site of the pregnancy. Neonatal morbidity, excluding major neonatal morbidity described as primary outcome, is defined as: Any health condition attributed to and/or aggravated by birth, assessed at the time point when the neonate is discharged from the hospital^21^ or—if discharged within 4 weeks after birth—at 4 weeks after birth, that has negative outcomes to the neonatal well-being (ie, IVH grade 1–2, PVL grade 1, mild BPD, NEC grade 1, ROP (any grade)) not necessitating laser therapy, hypoxic ischaemic encephalopathy, neonatal seizures, neonatal sepsis (culture proven), need for intubation on the delivery room, mechanical ventilation within the first 72 hours after birth, antibiotics within the first 72 hours after birth, spontaneous intestinal perforation necessitating surgery, surfactant treatment, Apgar score <7 after 5 min, severe metabolic acidosis (pH <7.05 and base deficit ≥12 mmol/L). This definition of severe metabolic acidosis is set at pH <7.10 and base excess ≥12 mmol/L in cases with only an umbilical vein sample (one available blood gas sample or the pH difference between two samples below 0.03^33^). Next to the study objectives described above, the data that is gathered in this study will be used to develop and verify mathematical models that aim at the prediction of time to (premature) birth and at automated detection of foetal movements.

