#### Prospective recruitment

Potential participants will be informed about the study by their obstetric healthcare professional when admitted to the hospital. First, the healthcare professionals will verify the inclusion and exclusion criteria (table 1), after which the women are added to the study using an encryption key. These women are part of the cohort study and receive standard care consisting of conventional intermittent CTG monitoring. A part of these women will be randomly sampled. This random sampling is conducted by the research team using a secure algorithm embedded in Research Manager (ISO 27001 certified). They will be offered the new treatment: continuous eCTG monitoring using the NFMS (figure 2). The women will either be part of the cohort study, thus receiving standard care consisting of conventional intermittent CTG monitoring, or they will be sampled for continuous eCTG monitoring using the NFMS. Appropriate explanation and written study information will be provided hereafter by the healthcare professional, and they will ask the researchers for further counselling. Non-sampled women will only receive information regarding the collection of their data in the cohort study. Sampled women will be informed about receiving continuous eCTG monitoring. A researcher will complete the informed consent (IC) procedure, including collecting written consent (for an example of the participant consent form, see online supplemental file 1). When the women do not wish to participate in the study, they will be excluded, their encrypted information will be obliterated and the exclusion will be anonymously documented. Once women are included, they are given the appropriate monitoring method. Five NFMS devices are available at the OHC of Máxima MC. When no NFMS device is available within 24 hours after sampling and inclusion, the sampled women will receive standard treatment within the study. For continuous monitoring, trained nursing staff will oversee device placement and signal quality checks during routine care. CTG traces are continuously displayed on a central monitoring system, where deviations from normal patterns trigger automated alarms to alert clinical staff. In addition, CTG traces are systematically assessed by physicians at least four times per 24 hours at predefined intervals, partly retrospectively, and more frequently if clinically indicated. These assessments follow a standard operating procedure (SOP) to ensure consistency and clinical relevance. If the eCTG recording does not provide sufficient signal quality for reliable monitoring, we will report this and, if needed, can be switched to standard CTG monitoring. This decision will be made on the clinical judgement of the attending gynaecologist. No literature was available on an acceptable signal loss threshold. The International Federation of Gynaecology and Obstetrics Guidelines advises switching monitoring methods in intrapartum monitoring when a signal loss threshold of 20% is reached.^35^ Based on this, a standardised protocol for switching to conventional CTG will be implemented when signal loss exceeds 20%, or when clinical judgement deems the eCTG trace insufficient for reliable interpretation. This protocol will be documented and monitored throughout the study. Women who decline to be part of the cohort will receive standard care: conventional CTG monitoring without data collection for research. All prospectively included women will receive a digital invitation to two digital surveys. Women are asked to fill in the first survey about their experience with the received monitoring method—EQ5D5L questionnaire^36^—on the first day after admission, and the second survey about their experience—D-QUEST^37^—on the last day of admission. Although the patient satisfaction surveys are administered at admission and discharge, all participants are followed up until (at least) 4 weeks postpartum. During this period, patients have the opportunity to share additional reflections or concerns with their care team, which may provide further qualitative insights into their experience with the monitoring method.

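### Patient questionnaires are tested unadjusted by default and adjusted only after an undefined imbalance is seen, in the comparison most exposed to selection by women who declined eCTG

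*Protocol article*

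**What the plan says.** The Study objectives section lists "satisfaction for both patient and caregiver" among the secondary objectives. The Statistical analysis section opens with a general rule: "For the primary and secondary outcomes, based on the demographics, characteristics of the women and their baseline outcomes, a propensity score will be created". It gives two reasons for the score. The first is "the group of women who are offered eCTG but receive CTG (either by choice or circumstances"; the second is the mixing of historical and prospective women.

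Later in the same section there is a separate rule for surveys: "For the data gathered from the questionnaires, standard statistical tests will be used", namely χ², t and Mann-Whitney tests. The conditional sentence follows: "A propensity score approach will be applied as well if large imbalances between characteristics are present between CTG and eCTG participants". No threshold for a large imbalance is given, and nothing says whether the adjusted result replaces the unadjusted one or stands beside it. The only decision criterion is general: "A p value of <0.05 is considered statistically significant unless otherwise specified".

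On who is surveyed, the Prospective recruitment section says: "All prospectively included women will receive a digital invitation to two digital surveys". Historical controls therefore contribute nothing to this endpoint.

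**The concern.** The analysis is by monitoring received, so random sampling does not protect the questionnaire comparison. A woman who is offered continuous monitoring and declines it moves into the CTG group, and her reasons may well bear on how she rates her monitoring. The plan recognises this bias and builds a score against it. For the questionnaires, however, it makes use of the score depend on an inspection of the data.

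That rule has two weaknesses. With a small CTG group, observed imbalance is a noisy guide to true imbalance. Several modest differences, none of them large alone, can also add up to a material bias without triggering adjustment. What is at stake is whether a reported difference in patient satisfaction reflects the monitoring method or the kind of woman who accepted it.

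**Working it through.** **Group sizes (Sample size section).** 335 women accept and receive eCTG, 37 sampled women decline it and receive CTG, 37 are non-sampled, and 1400 are historical. As a check that these are the plan's analysis groups: 335 against 37 + 37 + 1400 = 1474, at 11% v 17% and two-sided 5%, gives 80.1% power. This reproduces the stated 80%.

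**Share of decliners among controls.**
- Primary comparison: 37 / 1474 = 2.5%.
- Patient questionnaires: 37 / (37 + 37) = 37 / 74 = 50%.

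Sampled women for whom no device is free within 24 hours also receive CTG. The plan gives no number for them.

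**Precision of an imbalance check.** With full response (assumed), the standard error of a standardised difference is √(1/335 + 1/74) = 0.128. The plan gives no cut-off, so take 0.25 on any of eight independent covariates (assumed). The chance that at least one exceeds it is 1 − (1 − p)⁸, where p is the chance for one covariate:

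| True shift per covariate | p | Adjustment triggered |
|---|---|---|
| 0 | 0.052 | 35% |
| 0.05 SD | 0.070 | 44% |
| 0.10 SD | 0.125 | 66% |

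Such a check fires in about a third of trials with no true imbalance and misses 34–56% of trials with these real ones.

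**False-positive rate of the unadjusted test.** Assume no true effect and equal covariate weights, with multiple correlation R between covariates and score. If all eight shifts act in the same direction, the bias is R × shift × √8 SD. Dividing by 0.128 gives the displacement d, and the rejection rate is Φ(−1.96 + d) + Φ(−1.96 − d). For mixed directions, the rate is averaged over random signs.

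| R | Shift | Bias, same direction | Rejects, same direction | Rejects, mixed directions |
|---|---|---|---|---|
| 0.3 | 0.05 | 0.042 SD | 6.3% | 5.2% |
| 0.3 | 0.10 | 0.085 SD | 10.1% | 5.6% |
| 0.5 | 0.05 | 0.071 SD | 8.5% | 5.4% |
| 0.5 | 0.10 | 0.141 SD | 19.6% | 6.8% |

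A simulation of the same-direction case (20,000 trials per setting) gave 6.4%, 10.4%, 8.7% and 19.7%. Regression on the true covariates, standing in for the score, held 4.8–5.2%.

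**Extra error from having two tests.** In that simulation, counting a result as positive if either test was significant, with the second run only after the trigger, moved the rate as follows:
- no shift: 5.2% to 5.8% (R = 0.3) or 6.0% (R = 0.5);
- shift 0.05: 6.4% to 7.0%, and 8.7% to 9.9%;
- shift 0.10: 10.4% to 11.7%, and 19.7% to 21.4%.

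The addition is 0.6 to 1.7 points.

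**Second model.** A simulation with three covariates, an estimated propensity score, sandwich errors and a 0.2 cut-off (3,000 runs per setting) gave 3.3–5.6% for the adjusted test throughout. Under its stronger, same-direction selection, the unadjusted test rejected in 12–50%. The cut-off then fired in 80–98% of runs, so missed adjustment is mainly a problem of modest imbalances.

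**The case against.** The survey sentence can be read as a deliberate exception to the opening rule, since one of the score's two purposes, combining historical and prospective women, does not arise here. That is fair, and the point does not need an outright contradiction. The other purpose does arise, and more strongly than anywhere else in the study.

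A reader might infer that a difference will be declared on whichever test is significant. The text does not say so. The conditional sentence can also mean that the adjusted result takes over once imbalance is large, and on the figures above the second test adds little.

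A reader might also take 10–20% as the expected error. That needs all eight shifts to push satisfaction the same way; with mixed directions the excess nearly disappears.

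The threshold and the order of analyses could be settled in a full protocol or analysis plan that is not shown. That answers the missing definition. It does not answer the stated rule, which makes the unadjusted test the default.

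Finally, adjustment is not automatically safe. The main score spans both cohorts, and its listed covariates include duration of hospitalisation, which is determined after monitoring starts. This objection stands and shapes the fix.

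**Conclusion.** The point holds in limited form. For patient questionnaires the plan states a default that ignores the selection it elsewhere sets out to correct, in a comparison where about half of the controls, against about 2.5% in the primary comparison, are women who declined the intervention. A noisy and undefined imbalance check decides whether that is addressed, and no deciding result is named.

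The size of any bias cannot be derived from the document. Under the assumed shifts, the unadjusted false-positive rate lies between about 5–7% and about 6–20%, depending on whether the imbalances offset or reinforce one another. R, the shifts, the cut-off, the number of covariates and full response are all assumptions. Multiplicity is a minor part. The point concerns a secondary outcome, does not touch the primary analysis, and does not extend to the caregiver survey.

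**What to change.** State in advance, before questionnaire outcomes are examined, that the propensity-adjusted model is the single deciding analysis for patient questionnaires whatever imbalance is seen. Use the models the section already specifies: a general linear model with sandwich variance for scores and logistic regression for categorical items. Refit the score in the prospective women only, on covariates fixed before monitoring begins, leaving out duration of hospitalisation. Report the χ², t and Mann-Whitney results as descriptive.

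The cost is a few sentences of text, one extra score model and possibly a slightly wider interval. The change gives no protection against unmeasured reasons for declining eCTG, and the report should say so.
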